### Participant timeline {13}

The patients are enrolled, allocated and begin the intervention about the same date, which is at least 6 weeks prior to surgery.

The semi-structured interviews take place after ending the STRONG programme using an interview guide developed by the study team, based on the study aim, previous prehabilitation research [56] and concepts in the frameworks described above.

### Sample size {14}

Overall, we will include 42 patients. The power calculation regarding the main outcome is based on meta-analyses of quit rates after about 6 weeks at 70% (ranging 50–90%) [29, 30] after the intensive interventions like GSP for smoking and alcohol cessation intervention in the perioperative period as well as on studies reporting completion of physical exercise programmes at 66%, while the effect in the control groups were 15% (5–25%) [33, 57]. The corresponding lifestyle-related risk reduction will go from 100 to 30% in the intervention group and from 100 to 85% in the control group. Using an 80% power and 2 × alpha = 0.05, this would result in enrolment of 2 × 11 patients. However, the effect of obesity intervention is not known in patients with cancer undergoing major bladder surgery, but the number of patients with obesity seems low based on clinical experience; thus, a conservatively estimated sample size based on a lower effect of the intervention and allowing for dropouts would be 2 × 21 patients.

The number of participants in the interviews is determined by the concept of information power which will guide the adequate sample size. This entails an ongoing reflection during the study considering issues such as the aim of the study, sample specificity, use of a theoretical background and the chosen analytical strategy [58]. In this study, we propose to include about 8 patients from the RCT study and their relatives and clinical staff.

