## Statistical methods

### Statistical methods for primary and secondary outcomes {20a,b,c}

The effect of the intervention on risk reduction at surgery and SNAP improvement is analysed by Fisher’s exact test on an intention-to-treat basis. Estimates of the difference between treatment groups will be reported as relative risks (RR) with 95% confidence intervals (CI) and *p* values. Effects of the intervention Health-Related Quality of Life scores are analysed by Mann-Whitney’s *U* test. *p* values below 0.05 and CI not including the value 1 are considered significant. The analyses are done by Stata®.

For the interviews, the transcription, the triangulated analyses and data management will be conducted using NVivo QSR International.

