## Discussion

This study evaluates the risk reduction effect of combined intensive interventions for up to five unhealthy lifestyles in the preoperative period during chemotherapeutic treatment prior to radical bladder resection for urothelial cancer.

From a public health perspective, there is an effect of even brief and even very brief lifestyle intervention, which is therefore often recommended [60]. However, this effect is relatively small, though measurable and cost-effective at the population level and therefore important on the longer term.

By contrast, the surgical agenda characterised by fixed dates for surgery and focus on clear risk reduction within short time, thus moving the high-risk patient to a lower risk level for complications and faster recovery — already before the operation.

Therefore, the STRONG programme uses the highly effective intensive intervention, the GSP [42], that has proven significant quit rates of about 50% for smoking and risky alcohol intake at short term followed by a similar reduction of clinical complications in surgical settings [61]. They may also be followed by a long-term effect as well [29]. Unfortunately, the briefer interventions have a lower effect on lifestyles and until now no effect on complications [29].

In addition to the intensity of the intervention, also the aim of complete lifestyle change is of importance to receive a clear risk reduction prior to surgery. Reducing, but not quitting smoking or risky alcohol intake, does not significantly impact the complication rates [61, 62].

From a clinical perspective, it is relevant to get the most surgical risk reduction from an intervention and therefore put the focus on the unhealthy lifestyles followed by the highest risk, i.e. daily smoking, alcohol intake exceeding 2 drinks per day or 14 per week and malnutrition defined by the ESPEN surgical guidelines. However, when looking into co-existing risk factors, there seems to be an interaction on the risk, as shown for smoking and increasing BMI [63]. Therefore, it makes sense to evaluate the effect of the combined STRONG for all the five risk factors, in order to harvest the unused potential for risk reduction.

The STRONG programme has been developed in multi-professional collaboration, but it is intended to be feasible for delivery for individual patients by an especially trained nurse as part of the already existing patient journey in relation to surgery.

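### The 2 × 11 calculation does not match the planned Fisher's exact test (64% power, not 80%), so the unquantified margin built into 2 × 21 is smaller than it appears

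*Protocol article*

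**What the plan says.** Sample size {14} of the protocol article takes an intervention success rate from "quit rates after about 6 weeks at 70% (ranging 50–90"%) and a control rate from "the effect in the control groups were 15% (5–25"%). On the risk scale it expresses these as "from 100 to 30% in the intervention group and from 100 to 85% in the control group", which is 70% versus 15% success. From these rates it concludes: "Using an 80% power and 2 × alpha = 0.05, this would result in enrolment of 2 × 11 patients".

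The size actually enrolled is larger. Because the effect of obesity intervention in this population is unknown, the section adopts "a conservatively estimated sample size based on a lower effect of the intervention and allowing for dropouts would be 2 × 21 patients". It gives no value for the lower effect, the dropout rate or the power at 2 × 21. Recruitment {15} says only that few participants have left comparable trials.

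The statistical methods section {20a,b,c} says the risk-reduction outcome will be analysed by Fisher's "exact test on an intention-to-treat basis". The Discussion describes the programme on which STRONG is built as having "proven significant quit rates of about 50% for smoking and risky alcohol intake at short term".

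**The concern.** Fisher's exact test is conservative in small samples, so a size taken from an uncorrected normal or chi-square formula has less power than stated once Fisher's test is applied. With about a dozen patients per arm the gap is large.

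The enrolled size is 2 × 21, so what matters is how the step from 11 to 21 is read. A reader will take all ten extra patients per arm as protection against a weaker effect and dropout. If part of that increase only restores the 80% power already claimed, the real protection is smaller. Because neither the lower effect nor the dropout is quantified, the reader cannot tell how much is left. A non-significant result could then be over-read: the Discussion says that new strategies are required if these patients do not benefit.

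**Working it through.** **Inputs.** Success 70% versus 15%, two-sided alpha 0.05, power 80% and 2 × 11 then 2 × 21 come from Sample size {14}. Allocation 1:1 is from Trial design {8}. Fisher's exact test is from Statistical methods {20a,b,c}. The 50% rate is the Discussion's figure and also the lower end of the range in Sample size {14}. The 19 analysed per arm is my illustration of dropout (2 of 21, about 10%), since the article gives no rate.

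**Step 1: reproduce 2 × 11.** With p1 = 0.70, p2 = 0.15, difference 0.55 and mean 0.425:

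- Pooled formula: n = [1.960 × √(2 × 0.425 × 0.575) + 0.842 × √(0.70 × 0.30 + 0.15 × 0.85)]² / 0.55² = (1.370 + 0.489)² / 0.3025 = 11.4 per arm.
- Arcsine formula: h = 2·arcsin√0.70 − 2·arcsin√0.15 = 1.187, and n = 2 × (1.960 + 0.842)² / h² = 11.1 per arm.
- The uncorrected chi-square test has exact power 79.7% at 11 per arm. The continuity-corrected formula gives 15 per arm.

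So 2 × 11 is what a standard uncorrected method gives, to within rounding.

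**Step 2: power under the planned test.** Fisher power is the sum of Bin(x; n, p1) × Bin(y; n, p2) over all pairs (x, y) with two-sided Fisher p < 0.05. For 70% versus 15%:

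| n per arm | Fisher power |
|---|---|
| 11 | 63.7% |
| 12 | 72.2% |
| 13 | 79.1% |
| 14 | 77.5% |
| 15 | 79.6% |
| 16 | 84.4% |
| 19 | 92.9% |
| 21 | 93.8% |

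The first size above 80% is 16 per arm. Of the 21 − 11 = 10 patients added per arm, 16 − 11 = 5 restore the stated power, and 21 − 16 = 5 remain for a lower effect and dropout.

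**Step 3: what 2 × 21 covers against a 15% control rate.**

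| Intervention rate | 21 per arm | 19 per arm |
|---|---|---|
| 70% | 93.8% | 92.9% |
| 66% | 89.4% | 88.3% |
| 60% | 79.9% | 78.3% |
| 55% | 69.6% | 67.2% |
| 50% | 57.7% | 54.4% |

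At 50% versus 15%, 80% power needs 32 per arm (81.5%).

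**Step 4: sensitivity to the control rate at 2 × 21.** Over the stated 5–25% control range:

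- At an intervention rate of 50%, power is 91.1% with a 5% control rate, 57.7% with 15% and 26.1% with 25%.
- At the design rate of 70% with a 25% control rate, it is 75.7%.
- At 90% versus 25% it is 99.3%.

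**The case against.** The strongest reply is that 2 × 11 is an intermediate step and no trial of that size is being run. The enrolled 2 × 21 exceeds the 80% target under Fisher's test at the design rates, with room for some dropout. That stands. A reader might infer from the 64% that the trial is underpowered for its own assumptions, and the documents do not support that.

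Nor is 2 × 11 an arithmetic slip. It reproduces with a standard formula, and the fault is that the formula does not belong to the planned test.

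The 58% is also conditional. The Discussion's figure is a quit rate for smoking and risky alcohol intake, whereas the primary outcome needs a one-step improvement on only one of up to five lifestyles. A patient with several risk factors has several chances to succeed. As an illustration, assume two independent factors per patient, each with 50% versus 15%. The rates become 1 − 0.50² = 75% and 1 − 0.85² = 27.75%, and Fisher power at 2 × 21 is 81%. The article does not give the number of factors per patient, so this does not establish adequate power. It does show that 58% is one scenario and not a prediction. Sample size {14} does itself use quit rates as the proxy for this outcome, so the scenario is a fair one to report.

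Two further readings are tempting and fail. The Abstract's quit rates above 50% do not conflict with 70%. The 66% completion rate for exercise programmes measures adherence, but the calculation runs on 70% versus 15%, so removing it changes no result.

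The full protocol, which the article condenses, may hold the scenario behind 2 × 21. That excuses brevity. It does not make 80% power the right figure for 2 × 11 under the test the article names.

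**Conclusion.** The point holds as a moderate correction. The stated 80% power for 2 × 11 is about 64% under the planned test, and the matching size is 16 per arm. The trial as enrolled is adequate at 70% versus 15% (94%, or 93% with 19 per arm). Its margin is about half of what the step from 11 to 21 suggests. It reaches about 80% power down to roughly 60% versus 15%, with no dropout and a 15% control rate.

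Below that, power falls quickly. It is 58% at 50% versus 15%, if a single-factor quit rate is taken as the success rate of the primary outcome. At 50% it ranges from 91% to 26% over the article's own control range. A reader might conclude that the Discussion's figure refutes the 70% assumption. It does not: 50% lies at the lower end of the range that Sample size {14} already states. It does mark a lower effect that 2 × 21 does not cover at 80% power with a 15% control rate.

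**What to change.** Keep 42 patients and the planned analysis. In Sample size {14}:

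- Restate the calculation for Fisher's exact test: 70% versus 15% needs 16 per arm, and 2 × 21 gives about 80% power for 60% versus 15% with no dropout.
- State the lower effect and the dropout rate that 2 × 21 is meant to cover, with the Fisher power under both together.
- Give the power at 50% versus 15% (58%), say that it treats a single-factor quit rate as the primary-outcome rate, and show how it moves over the 5–25% control range.
- Add a sentence relating the 70% central value to the Discussion's figure of about 50%.

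The cost is one rewritten paragraph, with no extra patients and no change of test. The downside is that the stated margin looks less favourable.

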### Recruitment {15}

The patient flow at the department will ensure adequate enrolment to reach the target sample. All patients are evaluated for eligibility in the study period. Recruitment, intervention and follow-up take place during the daytime on working days and are planned together with the participants. The interviews can be conducted at the hospital or at home according to the wishes of the participant. From previous studies on the patient group, we have experienced that only few participants leave the lifestyle intervention trials [33, 48].

## Assignment of interventions: allocation

### Sequence generation {16abc}

After informed consent, the participants will be randomised by the project nurse to the intensive lifestyle intervention or standard care using a computer-generated block randomisation scheme [59]. The computerised randomisation system is accessible around the clock, and the use is logged. This ensures immediate randomisation of patients accepting participation and adequate allocation concealment. Block sizes vary from 2 to 5.

## Assignment of interventions: blinding

### Who will be blinded {17a}

It is rarely possible to blind intensive lifestyle intervention. The project data are kept away from the medical record system, though it cannot be guaranteed that the participant does not spontaneously tell the clinicians and the outcome assessor about the intervention group allocation. However, all biomarker analyses for validation and the statistical analyses will be performed blinded. Likewise, the measurement of postoperative complications is done by a blinded urologist not involved in the project.

### Procedure for unblinding if needed {17b}

The design is open label with outcome assessors and data analysts being blinded so unblinding will not occur.

## Data collection and management

### Plans for assessment and collection of outcomes {18a}

Project staff will collect data; please see Tables 2 and 3. The data for analyses are performed blinded and there will be no personal identification in the presentation of results. Complications will be registered using predefined definitions by two assessors blinded to the allocation group.

**Table 2 Tab2:**
[figure not shown]
Schedule of enrolment, interventions and assessments for all patients (*included in the frailty definition)

**Table 3 Tab3:** Further weekly assessments in the STRONG intervention group

Assessments (STRONG group)	Meet 1	Meet 2	Meet 3	Meet 4	Meet 5	cont. until surgery
Smoking						
Cigarettes per day (N^o^)	X	X	X	X	X	X
NRT (mg) as craving reducing medicine	X	X	X	X	X	X
Validation by CO concentration (breath)	X	X	X	X	X	X
Alcohol						
Alcohol per week (units 12 g, TLFB)	X	X	X	X	X	X
Alcohol concentration (breath test)	X	X	X	X	X	X
Alcohol biomarkers (blood + urine)	X	X	X	X	X	X
Withdrawal symptoms (CIWA-R)	X	X	X	X	X	X
Use of AWS prophylaxis (mg)	X	X	X	X	X	X
Nutrition						
Food intake according to plan	X	X	X	X	X	X
Appetite level /healthy days	X	X	X	X	X	X
Weight and bio-impedance	X	X	X	X	X	X
Validation by nutrition profile in blood	X	X	X	X	X	X
Physical activity						
Physical activity according to plan	X	X	X	X	X	X
Steps walked per day	X	X	X	X	X	X
Validation by 6-min walk test	X	X	X	X	X	X
Timed Up and Go test	X	X	X	X	X	X
Hand grip strength	X	X	X	X	X	X

### Plans to promote participant retention and complete follow-up {18b}

All meetings are planned to take place together with the usual contacts in the patient journey. In case of dropout, we will follow our previous procedure and ask the patient for written consent to allow follow-up in the medical record system. This is included in the application for the Scientific Ethical Committee.

### Data management and confidentiality {19,27}

The data are collected and securely stored in the Redcap system using a project ID for each participant instead of personal identifiable information, as recommended by the Capital Region of Denmark, where the trial takes place. The key between the project ID and the personal identification is stored under a double lock. Only the project group have access to the data.

The conduction of the project follows the Danish Data Protection Agency guidelines of the European GDPR before, during and after the trial. After ending the trial, the personal information is destroyed and the other data are stored at the Danish National Data Archive — also fulfilling the Danish and European guidelines for data management and protection.

### Plans for collection, laboratory evaluation and storage of biological specimens for genetic or molecular analysis in this trial/future use {33}

In this study, all patients have a blood test for the identification of alcohol and/or smoking biomarker and for nutrition profile analyses (2 × 5 ml whole blood and 2 × 2 ml EDTA plasma, 2 × 2 ml citrate plasma, 2 × 2 ml serum, 5 × 2 ml urine): B-haemoglobin, B-MCV, P-gamma GT, P-Asat, P-bilirubin, p-albumin and p-protein. Of those, blood (10 ml) and urine (5 × 2 ml) will be sampled and stored for later identification of alcohol biomarkers (PetH, CDT and U-EtG).

The aim is to validate the self-reported data on lifestyle outcomes. The analyses of biomarkers are performed together for one factor at a time, mainly after collection of all samples. Therefore, it is necessary to collect and store the samples during the project period at the Parker Institute, Bispebjerg-Frederiksberg Hospital. The samples will be destroyed before 31.12.2030.

All analyses are expected to be performed locally at the Parker Institute, Bispebjerg-Frederiksberg.

The data handling is performed in agreement with GDPR, and the project is registered at the Data Protection Agency before start.

During the project period, new markers may be developed, and we would therefore keep half of the samples for future analyses of biomarkers related to measurement of markers for risk reduction at surgery in the future. The participants are separately asked about giving informed consent for that, understanding that a future measurement and data handling is performed in agreement with GDPR.

## Statistical methods

### Statistical methods for primary and secondary outcomes {20a,b,c}

The effect of the intervention on risk reduction at surgery and SNAP improvement is analysed by Fisher’s exact test on an intention-to-treat basis. Estimates of the difference between treatment groups will be reported as relative risks (RR) with 95% confidence intervals (CI) and *p* values. Effects of the intervention Health-Related Quality of Life scores are analysed by Mann-Whitney’s *U* test. *p* values below 0.05 and CI not including the value 1 are considered significant. The analyses are done by Stata®.

For the interviews, the transcription, the triangulated analyses and data management will be conducted using NVivo QSR International.

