### Eligibility criteria {10}

Inclusion criteria: Patients > 18 years, at least one of the five SNAP factors (defined below) and scheduled for radical cystectomy (RC) due to bladder cancer and referral to neo-adjuvant chemotherapy preoperatively
“Smoking”: daily smoking — no limitations [29]; validated by carbon monoxide (CO) in the breath test“Obesity”: BMI above 30 [46], validated by weight and height“Malnutrition”: based on ESPEN guidelines for surgery including albumin concentration in blood [6]“Risky drinking”: > 2 standard drinks per day (in average; 1 drink = 12 g ethanol), identified by timeline follow-back (TLFB) [47], and validated by alcohol biomarkers (carbohydrate-deficient transferrin (CDT), plasma phosphatidylethanol (P-Peth) and urine ethylglucuronide (U-EtG))“Physical inactivity”: < 30 min physical activity per day or 3.5 h per week

Exclusion criteria: pregnancy and breastfeeding as well as allergy and other contra-indications to pharmaceutical support, exercise or nutritional intervention; inability to give informed consent (e.g. low age, severe mental illness including delirious conditions, consciousness issues, local language challenges and similar) and withdrawal of informed consent.

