### Outcomes {12}

#### Risk reduction at surgery from changes in lifestyle

Primary outcome: Number of patients with surgical risk reduction of at least 1 step for 1 or more risky lifestyles on the ASA-score [51] after 6 weeks which is the end of the intervention.

Secondly: Number of patients without their preoperative risky lifestyles at 6 weeks after inclusion, at surgery and at 6-week and 6-month follow-up postoperatively:
Successful smoking cessation, validated by CO in the breath test and U-cotinineMalnutrition: Not at risk of malnutrition (ESPEN surgical guidelines, incl. albumin concentration) [6]Obesity: body mass index (BMI) < 30 or at least 5% loss of body fat mass and max 10% for obesity at 6 weeks (0.5–1 kg/weekly and below 1% gain of body fat mass at 6 months (without developing malnutrition) [52]Successful alcohol cessation at 6 weeks and intake below risky limits at 6 months, validated by CDT, P-Peth and U-EtGPhysical activity at least 30 min per day or 3.5 h per week and 6-min walk test (6MWT) > 500 m

Number of patients with any reduction of any of their lifestyles, i.e. reduced number of cigarettes, amount of alcohol intake and body fat mass, level of malnutrition as well as increased body-muscle mass, minutes of physical activity per day and 6MWT. Number of patients with reduced frailty level, measured by Lammers definition [22].

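### Stratifying the primary exact test by number of SNAP factors at entry would be a cheap, modest gain in power and in robustness to chance imbalance

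*Protocol article*

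**What the plan says.** - **Eligibility criteria {10}:** a patient must have "at least one of the five SNAP factors", so the number of factors at entry runs from one to five and is known for everyone.
- **Outcomes {12}:** the primary outcome counts patients with a risk reduction of "at least 1 step for 1 or more risky lifestyles" on the ASA-score at 6 weeks.
- **Sequence generation {16abc}:** allocation is made "using a computer-generated block randomisation scheme" with varying block sizes. No stratification factor is named.
- **Statistical methods {20a,b,c}:** "The effect of the intervention on risk reduction at surgery and SNAP improvement is analysed by" Fisher's exact test, with relative risks and 95% confidence intervals. No adjustment or stratification is named.
- **Sample size {14}:** success is taken as 70% (range 50–90%) with intensive intervention and 15% (5–25%) in controls. "Using an 80% power and 2 × alpha = 0.05, this would result in enrolment of 2 × 11 patients", which is then raised to 2 × 21 for a lower effect and dropouts, neither of them quantified.

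**The concern.** An outcome met by improving on any one of a patient's risky lifestyles gives a patient with three factors more routes to success than a patient with one. If so, the number of factors at entry is prognostic for the primary outcome. With 21 per arm it can differ noticeably between arms by chance, and the stated test takes no account of it. What is at stake is some power, mainly if the true effect lies at the low end of the plan's range, and a result that depends partly on how a known baseline variable happened to split.

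**Working it through.** **Inputs.** From Sample size {14}: success rates of 70% (low end 50%) v 15% (high end 25%), two-sided alpha 0.05, 21 per arm. Assumed, because the protocol gives neither: the mix of factor counts, and independent success on each factor.

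**1. The plan's own figure.** Pooled two-proportion formula for 70% v 15%, mean 0.425:

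n = [1.96 × √(2 × 0.425 × 0.575) + 0.842 × √(0.70 × 0.30 + 0.15 × 0.85)]² / 0.55² = (1.370 + 0.489)² / 0.3025 = 11.4, so 12 per arm.

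The arcsine formula gives 11.1. The stated 2 × 11 is therefore reproduced. At 11 per arm exact power is 79.7% for the uncorrected chi-square test but 63.7% for Fisher's test, which shows how conservative Fisher's test is at these sizes. The step to 2 × 21 cannot be derived and is taken as given.

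**2. Fisher's test at 21 per arm (exact enumeration).** 93.8% at 70% v 15%, 57.7% at 50% v 15%, 26.1% at 50% v 25%.

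**3. Model for factor count.** A patient with K factors succeeds with probability 1 − (1 − p)^K, with p set in each arm to give the overall rate. With 40/35/25% of patients having 1/2/3 factors, success is about 33/55/70% v 9/16/23%. Check: 0.40 × 33 + 0.35 × 55 + 0.25 × 70 ≈ 50, and 0.40 × 9 + 0.35 × 16 + 0.25 × 23 ≈ 15.

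**4. Simulated power (%), 21 per arm.** The last column stratifies on a label unrelated to outcome, to separate the effect of stratifying as such from the effect of factor count.

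| Mix of factor counts | Rates | Fisher | Exact, stratified by count | Exact, stratified by random label |
|---|---|---|---|---|
| 1/2/3: 40/35/25% | 50 v 15 | 58.3 | 63.8 | 61.5 |
| 1/2/3: 40/40/20% | 50 v 15 | 57.6 | 64.3 | 61.3 |
| 1/2/3: 50/30/20% | 50 v 15 | 57.8 | 64.9 | 61.6 |
| 1/2: 50/50% | 50 v 15 | 57.8 | 63.8 | 61.6 |
| 1/2: 80/20% | 50 v 15 | 57.7 | 62.1 | 61.2 |
| 1/2/3: 40/35/25% | 70 v 15 | 93.6 | 96.1 | 94.4 |
| 1/2: 50/50% | 70 v 15 | 93.8 | 96.0 | 94.9 |
| 1/2: 80/20% | 70 v 15 | 93.8 | 95.4 | 94.8 |

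Total gain at 50% v 15% in these rows: 4.4 to 7.1 points (about 4 to 8 over all mixes tried). Example split, 40/40/20%: 61.3 − 57.6 = 3.7 points from the random label, and 64.3 − 61.3 = 3.0 from factor count. For 80/20%: 3.5 and 0.9. At 50% v 25% the stratified test reaches about 31–34% against 26%. True size is about 2% for Fisher's test and about 2.5–3.4% for the stratified test.

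**5. Like with like.** At 50% v 15% the asymptotic Cochran-Mantel-Haenszel test has 70–72% power and the unadjusted chi-square test 72%. Once discreteness is removed from both sides, adjustment brings little.

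**6. Chance imbalance.** With 60% of patients having two or more factors, the 95% range for that share is ±1.96 × √(0.24/21) = ±0.21 in one arm. At 70% overall success the model gives about 53% with one factor and 81% with two or more, so the STRONG rate moves by about 0.21 × 0.28 = 0.06 at that limit. At 50% v 15%, about 13% of simulated trials left STRONG more than 15 points below control in the share with two or more factors. In those, Fisher's power was 44% and the stratified test's 64%. With an equal imbalance in favour of STRONG they were 74% and 66–67%.

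**The case against.** The stated test is valid and conventional for 42 patients, and its p value already allows for chance imbalance. Covariate adjustment is often left to a full protocol or analysis plan that is not shown. All of this stands: nothing in the article is wrong or contradictory here. The point concerns a test that the article does name for its primary outcome.

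The prognostic value of factor count is also modelled, not documented. Explanation for the choice of comparators {6b} says it is unknown how far patients can change several lifestyles at once. The Discussion reports that, in another patient group, participants with several risky lifestyles could not follow all the separate interventions. The Introduction names only alcohol, smoking and obesity as lifestyle details in the ASA-score, so each SNAP factor may not count as a further chance of success. This limits how firmly any gain can be claimed. It does not make the change harmful: with no prognostic value at all, the stratified test still went from 56.8% to 60.7%, through reduced discreteness.

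A reader might infer that ignoring factor count itself costs about 6 points of power. The random-label comparison contradicts this, because over half of the gap appears without any prognostic information. A reader might also call factor count the strongest predictor of the outcome. The documents give no success rate by number of factors, and the simulated R-squared is only about 0.03–0.11. Nor does chance imbalance move the STRONG rate by 8 points: that applies the between-arm range of ±30 points to a single arm.

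**Conclusion.** The point holds as an optional improvement in efficiency and robustness, not as a bias or an error. At 21 per arm the stratified exact test gains about 4–8 points at 50% v 15%, of which about 3–4 come from easing Fisher's discreteness and about 1–3 from factor count. At the planning rates of 70% v 15% the gain is about 1–3 points. Size stays below 5%. The gain at the low end leaves power near 62–65%, so the shortfall there remains. These figures rest on assumed factor mixes and on independent success per factor. The direction is more secure than the size, since the stratified test lost no power under any mix or dependence tried.

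**What to change.** Before any outcome data are seen by treatment group, state that the primary test is the exact conditional (Mantel-Haenszel type) test stratified by number of SNAP factors at entry, one v two or more. Report a Mantel-Haenszel relative risk with its 95% CI. Keep the unadjusted Fisher's test as a sensitivity analysis. Any power gain should be quoted as a range with its assumptions.

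The cost is one sentence of analysis text and minor programming; the stratum comes from eligibility data already collected. The downside is that the relative risk becomes a stratum-weighted one. The change must be pre-specified, because adopting it after an imbalance has been seen would not be credible.

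### Fisher's exact test is valid but conservative at 21 per arm (true two-sided error at most 2.3% against 5%); Boschloo's exact test would gain power at no cost in patients

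*Protocol article*

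**What the plan says.** The section on statistical methods for primary and secondary outcomes fixes the test for the binary outcomes: "risk reduction at surgery and SNAP improvement is analysed by Fisher’s exact test on an intention-to-treat basis". Group differences are to be reported as relative risks with 95% confidence intervals and p values. The decision rule is that p "values below 0.05 and CI not including the value 1 are considered significant". The method for the interval is not given, and Stata is the named software.

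The Sample size section takes 70% success with the intervention (range 50–90%) and 15% in the control group (range 5–25%), and continues: "Using an 80% power and 2 × alpha = 0.05, this would result in enrolment of 2 × 11 patients". It then raises the number, because "a conservatively estimated sample size based on a lower effect of the intervention and allowing for dropouts would be 2 × 21 patients". Neither the lower effect nor the dropout rate is given a value, and the section does not say which test the calculation assumes.

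**The concern.** Fisher's test conditions on the total number of responders. In small arms the conditional distribution has few possible values, so the rule p < 0.05 is met under the null hypothesis much less often than 5% of the time. The unused error costs power. In a trial of 42 patients that was enlarged because a smaller effect was thought possible, that power may matter. The same test serves the primary outcome and the binary secondary outcomes.

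Results of 11 vs 4, 12 vs 5 or 13 vs 6 responders out of 21 would be non-significant under Fisher's test, although an exact test that holds the 5% level rejects the null hypothesis for each of them.

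**Working it through.** **Inputs.** Success rates of 70% and 15% with their ranges, two-sided alpha 0.05, 80% power and 21 per arm all come from the Sample size section. Fisher's test and the significance rule come from the Statistical methods section. Assumed here: the lower effects, since none is stated; all 21 per arm analysed unless noted; and a Wald interval on the log relative risk where an interval is needed.

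**Step 1: the plan's own figure.** The pooled normal approximation without continuity correction is

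n = [z₀.₉₇₅·√(2p̄(1−p̄)) + z₀.₈₀·√(p₁(1−p₁)+p₂(1−p₂))]² / (p₁−p₂)²

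With p₁ = 0.70, p₂ = 0.15 and p̄ = 0.425:

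n = [1.960·√0.48875 + 0.842·√0.3375]² / 0.55² = 11.4

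The arcsine formula gives 11.1. The stated 2 × 11 is therefore reproduced to within rounding, by a formula that does not describe Fisher's test. Under Fisher's test, 11 per arm gives 64% power, and 16 per arm are needed to pass 80%. The step to 2 × 21 cannot be reproduced because its inputs are not stated.

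**Step 2: true error at 21 per arm.** Enumerate all 22 × 22 tables. For a common rate p, the error is the sum of Bin(x; 21, p)·Bin(y; 21, p) over the rejected tables (x, y). Maximise this over p.

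- Fisher, p < 0.05: maximum 2.34%, near p = 0.23 or 0.77, and about 2.0% at p = 0.4 to 0.5. At 19 per arm the maximum is 2.8%.
- Boschloo (Fisher's p used as the test statistic, cut-off about 0.093): maximum 4.81%.

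Boschloo's rejection region contains Fisher's, so its power cannot be lower. Examples out of 21 per arm:

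| Responders | Fisher p | Boschloo p | RR (Wald 95% CI) |
|---|---|---|---|
| 11 vs 4 | 0.052 | 0.027 | 2.75 (1.04–7.27) |
| 12 vs 5 | 0.058 | 0.032 | 2.40 (1.03–5.62) |
| 13 vs 6 | 0.062 | 0.038 | 2.17 (1.02–4.61) |

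In these tables the two halves of the protocol's rule disagree: the interval excludes 1, but Fisher's p exceeds 0.05.

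**Step 3: power at 21 per arm.** This is the same sum with the two rates set apart. The last column requires both the test and the Wald interval to be significant.

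| Rates | Fisher | Boschloo | Gain, points | Joint rule: Fisher to Boschloo |
|---|---|---|---|---|
| 70% vs 15% (stated) | 93.8% | 96.9% | 3.1 | gain 2.9 |
| 60% vs 15% | 79.9% | 87.4% | 7.5 | 79.7% to 85.5% |
| 55% vs 15% | 69.6% | 79.2% | 9.7 | 69.1% to 75.3% |
| 50% vs 15% | 57.7% | 68.9% | 11.3 | 56.7% to 62.2% |
| 45% vs 15% | 45.0% | 57.0% | 11.9 | 43.2% to 47.2% |
| 70% vs 25% | 75.7% | 84.7% | 9.0 | gain 8.9 |
| 60% vs 25% | 50.1% | 62.5% | 12.4 | gain 11.7 |
| 50% vs 5% | 91.1% | 95.2% | 4.1 | gain 0.3 |
| 90% vs 15% | 100% | 100% | 0 | 0 |

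Gains are taken from unrounded values. For scale, Fisher's test at 50% vs 15% needs 25 to 26 per arm (67.6% to 70.6%) to match Boschloo's 68.9% at 21.

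**Step 4: fewer patients analysed.** At 19 per arm, Boschloo's gain at 45–60% vs 15% is 4 to 10 points on the p value alone, and under 1 point on the joint rule.

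**The case against.** Fisher's test is standard, pre-specified and valid. A 5% level is a ceiling, and a test that stays below it contradicts nothing. Whether to condition on the total number of responders is also a long-standing disagreement among statisticians. All of this stands, and it is why the point is one of efficiency.

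A reader might infer that the plan gives away 7 to 12 points of power in general. The documents do not support that. At the only contrast the protocol states, the loss is 3.1 points and Fisher's test already has 93.8% power. At 66% vs 15% (66% being the exercise-completion figure in the Sample size section) the loss is 4.8 points. A loss of 7 to 12 points needs an assumed success rate of about 45–60% against 15%, or a 25% control rate with 60–70% on the intervention. Most of these values lie inside the protocol's quoted ranges, and 45% lies just below them, but the protocol adopts none of them as its lower effect.

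Two further limits stand. Under the joint reading of the significance rule, changing the test alone recovers only part of the gain. The figures are also specific to Boschloo's test: Barnard's test with the pooled z statistic gains about 6 to 8 points at 45–60% vs 15%.

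What the objection does not remove is that Boschloo's test holds the same 5% ceiling and is at least as powerful at the same number of patients.

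**Conclusion.** The point holds as a cheap improvement. At 21 per arm Fisher's test uses at most 2.3% of the planned 5%, and Boschloo's test uses 4.8%. The gain in power is about 3 points at the stated 70% vs 15%, and 7.5 to 11.9 points at an assumed 45–60% vs 15%. It is relevant because 2 × 21 was chosen to allow for a lower effect, and Fisher's power drops to 79.9% at 60% vs 15% and 57.7% at 50% vs 15%.

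The size rests on 21 per arm analysed, on the assumed rates, and on the p value alone deciding. If a Wald relative-risk interval must also exclude 1, the gain at 45–60% vs 15% is about 4 to 6 points with 21 per arm and under 1 point with 19.

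**What to change.** Before any unblinding, amend the section on statistical methods for primary and secondary outcomes, and the analysis plan if there is one, as follows:

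- Replace Fisher's exact test by Boschloo's unconditional exact test, two-sided at 5%, for the primary and the binary secondary outcomes.
- Make its p value the sole criterion of significance for these outcomes. Without this, much of the gain may be lost to the interval condition.
- Report the relative risk with its 95% confidence interval as the estimate, and Fisher's p value as supportive.

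The cost is a few sentences. No patients, visits or measurements are added. The downsides are that software beside Stata may be needed (the test is available in Python's scipy, for example) and that readers know the test less well than Fisher's.
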